**Fig. 2 Fig2:**
[figure not shown]
Flow chart of hybrid trial

We will systematically map barriers and strengths identified in Task 1 to USM implementation provided by diverse school and district representatives (i.e., food service providers, teachers, administrators, students, and parents) on to potential strategies based on prior work [58]. The goal of establishing performance objectives (Task 2) will be determined by our findings from Task 1 and by the key goal of increasing student participation in USM. For Task 3, strategies can be from one of many categories including planning (e.g., building stakeholder buy-in); education (e.g., training implementers); financial (e.g., incentives); structural (e.g., create teams); management (e.g., audit and feedback); or policy-related (e.g., licensure standards) [37]. Instead of the initial compilation of strategies developed for clinical settings, which use clinical terms (i.e., patients, providers), [37] our team will primarily consult strategy compilations tailored to the education [58] and community settings [59]. This process ensures we are following the most recent literature and guidance based on pragmatic trials. Grounded in GTE constructs, one potential implementation strategy from the “planning” category could be to assemble a group of students for an advocacy group, who would take a leading role in promoting school meal participation and collaborate with school food service. For Task 4, materials and protocols will be developed grounded with specific attention to the four GTE constructs [7]. These materials will outline what messages, methods, and materials are needed to carry out the chosen strategy through an equity lens. For example, if “planning” is the implementation strategy, specific communication practices may be created to recruit students and engage them in leadership activities based on needs in Task 1 [7].

#### Recruitment and engagement

All schools who participated in Task 1 [47] will be re-engaged and invited to participate in the next phase of the project, with additional schools recruited in collaboration with our CAB and the district to secure a sample of 4 schools. We will ask all schools to sign a collaboration agreement (See additional file 1) that states they agree to be involved in the project to be randomized to the first pilot or the waitlist comparison condition. Once received, we will block randomize schools by pairing the sample (2 in each group) based on characteristics such as geographic location, size, mode of food service (i.e., satellite or full-service kitchen), and student/family demographics.

Grounded in the GTE and EPIS frameworks [7, 53], this implementation mapping aim will be completed with representatives (at least 3) and students from each of the 2 intervention schools. We will meet with pilot school principals early in the process to identify suitable individuals who are invested in the school meals program; necessary individuals to recruit are administrators (i.e., principals) and food service providers given their essential roles in steering meal provision practices. We will aim to recruit at least 1 student, parent, and teacher from each school through distributing flyers (See additional file 2) to schools and targeted sampling through the principal and other administrators to ensure we find individuals who are committed to the process and meetings. We will hold ~ 5 meetings during/after school (based on school team preference) roughly 3–4 weeks apart to accomplish Tasks 2–4 and prepare for full rollout. For all participants, we will distribute informed consent forms (and assent for students) to facilitate data collection and provide a $25 gift card per participant per meeting attended.

#### Data collection procedures and measures

We will utilize predominantly qualitative methods for this strategy development aim through a series of semi-structured meetings with school representatives. Each planning meeting will accomplish part of a mapping task (Tasks 2–4); workbooks will be developed by the research team to distribute to all attendees to facilitate discussion. These workbooks will be developed through review of prior examples of successful toolkits for implementation strategy development [60] in collaboration with our CAB and the school district. Meetings for Task 2 (identify outcomes) will focus on reviewing data from Task 1 (needs assessment), getting feedback from school representatives on findings, and setting goals for implementation. Example prompts will include: “What findings shocked you or stood out?” and “what do you want to see change with the school meals program?” to arrive at clear goals and desired improvements for the program.

Meetings for Task 3 (develop strategies) will focus on taking the desired goals and objectives and developing strategies for improving implementation. We will facilitate refining ideas and asking representatives to collectively rate the difficulty and complexity of chosen strategies (i.e., easy, moderate, hard) and cite potential barriers to implementation. Example prompts for discussion include: “What strategies or practices do you think we could try to address some of these challenges to school meals?” and “What barriers would we need to consider for implementing this strategy?”. Finally for Task 4 (develop protocols) we will collectively finalize the chosen strategies and begin to “backwards plan” for these by discussing what materials/supplies, funding, training, and other support is needed to execute these strategies (prompt: “what do we need to implement this strategy?”) and to decide on the timing, intensity, and frequency of implementing them. Example prompts include: “What funding do we need to get this strategy/project implemented?” and “How often/much are we going to do this [strategy]” for each of the strategies the group selects to test out. We will also discuss who will lead the deployment of each strategy. This will facilitate creation of protocols in alignment with reporting recommendations for implementation strategies [61]. We will record all meetings and have them professionally transcribed verbatim.

#### Analyses

Aligning with the purpose of this aim, we will use a deductive coding process to ensure development of strategies grounded in EPIS and GTE frameworks, followed by inductive coding to generate overarching themes of the strategy development process. We will utilize MAXQDA TeamCloud software [62] to conduct team coding of all meeting transcripts and workbook entries from participants. For deductive analyses, we will create a 3-level coding structure to generate codes for 1) each phase of EPIS (separate codes for barriers and facilitators), 2) each construct (i.e., inner, outer setting, innovation factors, bridging factors), and 3) each quadrant of the GTE with “barrier” and “potential strategy” within each component, similar to prior uses of EPIS for strategy development [63–65]. This will facilitate coding of the transcripts to a code within each level (if applicable) or a code within 1 or 2 levels depending on the data and group decision. For example, during initial mapping meetings a school/district representative may bring up challenges to addressing student stigma because of the limitations with the menu or current meal service format. This kind of example would be coded under “Exploration-Barriers” (EPIS) and under “Reduce Deterrents-Strategy” (GTE) because of the alignment with both our implementation process and health equity frameworks. Analyzing our data in this multifaceted way will hold the research team accountable for spotting equity “blind spots” and for matching pragmatic/logistical challenges with potential strategies in later meetings.

The team will conduct parallel coding of the first 1–2 transcripts to ensure intercoder reliability, followed by consensus coding in pairs to resolve coding disagreements. We chose this process because it facilitates more accurate coding given a relatively small sample size (*n* = 2 schools in first pilot) with large volumes of data for each school (roughly 1.5 h per meeting; ~ 5 meetings total per school yielding ~ 10 transcripts) requiring more in-depth analyses. Use of the GTE framework for implementation strategy development has not been documented before; thus, the more in-depth approach will take longer than using EPIS alone. We will refer to the notes taken in each meeting to support and refine the coding protocol over time.

### Aim 2: evaluate implementation and student-level outcomes of the strategy using a hybrid type III implementation-effectiveness design

Following the hybrid type III approach, [56] a longitudinal convergent (Quantitative–Qualitative) mixed-methods design will investigate the impact of this trial. Primary implementation outcomes of penetration/reach will be calculated through analyzing participation rates from breakfast and lunch service across the implementation period. We will create an implementation costing measure to calculate the financial cost of each implementation strategy. Additional outcomes of acceptability (i.e., are representatives satisfied with this strategy?), feasibility (i.e., was this simple to carry out?), and sustainability (i.e., could this be maintained?) will be assessed from the perspective of implementers. Implementation objectives identified in Task 2 will be evaluated through brief, semi-structured interviews with implementing representatives*.* Secondary student health outcomes of weight status, food insecurity, and dietary behaviors will be analyzed over the 2-year implementation period.

#### Participants and procedures

Intervention school teams will receive coaching during the implementation phase with monthly check-in meetings at school sites or via phone/Zoom if necessary (~ 15–30 min) to support implementation efforts and retention of schools across the intervention period. Implementation leaders and other front-line implementers (i.e., food service staff) from intervention schools will be asked to complete surveys and brief interviews to address implementation outcomes. Administrators and food service providers will be asked to participate in interviews which will facilitate the development of the costing measure. Penetration and behavioral data for all 4 schools will be collected before Aim 1 begins and throughout study completion. Table 1 illustrates the implementation (in green) and behavior/health outcome (in blue) measures we will collect, the source, data collection period, and the timing/frequency of these measures for the hybrid type III implementation-effectiveness study.

**Table 1 Tab1:** Hybrid type III study: overview of variables, data source, collection period, and timing/frequency of data collection

	**Variable**	**Source**	**Data Collection Period**	**# Time Points/Frequency**
**Implementation Outcomes**	Penetration (Meal Participation)	Division of Food Services	Daily for Breakfast and Lunch	Monthly Average (%) per student
	Cost	Cost Survey and Interview	Fall and spring each year	4 (2 in each trial year)
	Acceptability	Implementation Survey	Fall and spring in first year	2
	Feasibility	Implementation Survey	Fall and spring in first year	2
	Sustainability	Implementation Survey	Fall and spring each year	4 (2 in each trial year)
	Implementation Determinants	Check-in Meetings	Monthly	18 (9 each year)
**Behavior/Health Outcomes**	Race, ethnicity, economic disadvantage	District database	Fall of each year	2
	Weight Status/BMI	Office of Health Services	Fall of each year	2
	Student hunger, self-reported participation, dietary behavior	Office of Research and Evaluation	Spring of each year (student survey)	2
	Attendance	District Database	Daily for each student	Monthly Average (%) per student

#### Data collection and primary outcomes

The number of breakfast and lunch meals served (linked to student ID) will provide data on penetration, facilitating assessment of equitable access to low-income students. For cost of implementation, Our team will develop a bottom-up costing strategy and measure the costs for each implementation strategy that results from the mapping process, following guidance from experts in economic evaluation of implementation [49, 66] and in collaboration with our CAB and school district partners. We will do this by establishing categories of resource use for each strategy (e.g., labor, materials, travel) and developing initial measures to capture time and effort of all implementing participants at the school sites. We will then conduct a budget impact analysis and costconsequence analysis to enhance understanding of the value for each strategy and determine potential for scale-up. Validated surveys adapted for the school context by the principal investigator (see additional file 3) will provide data on acceptability, feasibility, and sustainability of the implementation strategy by each member of the implementation team [67–69]. Finally, brief (i.e., 20–30 min) interviews will be held with key implementing representatives (identified in Task 1) to identify the degree to which implementation objectives were met grounded in the GTE toward the end of the first year of implementation [38, 44, 45]. We will also ask about overarching facilitators and barriers during these interviews, mapping determinants to the Implementation and Sustainment phases of EPIS. To support replicability of our protocol, all surveys, interview guides, coding materials, and other pertinent documents will be made publicly available on our lab website and through article publication.

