This pilot intervention will utilize an evidence-based process (i.e., implementation mapping) [38] and test primary implementation outcomes of penetration and cost, [48, 49] and secondary impact on student health outcomes (i.e., weight status, food security, dietary behaviors).

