The GTE [7] and the Exploration, Preparation, Implementation, Sustainment (EPIS) [53] frameworks will ground Aim 1 (Tasks 2–4) to guide the selection and tailoring of implementation strategies and protocols [7, 54]. The GTE was developed to inform operationalization of equity principles and concepts in PSE approaches related to obesity, in partnership with members of the community of interest. GTE guidance prompts for identifying and addressing intervention design features and contextual variables to improve equity impact, accounting for individual and community-level resources and capacity [7]. The EPIS framework [53] conceptualizes key phases of Exploration (deliberating ways to innovate/the innovation), Preparation (planning for implementation), Implementation (the process of implementing), and Sustainment (maintaining implementation) that guide and describe the implementation process. Similar to CFIR, EPIS provides a set of constructs among key domains of outer context (outside the school system) and inner (within school) context across these phases, bridging factors that span across inner and outset settings, innovation factors, and role of innovation adopters. Together, these frameworks will support the co-development process, ensuring that strategies and protocols developed are grounded in addressing inequities in access (GTE), and that we have a strong structure (EPIS) that facilitates consideration of key determinants and processes over discrete phases of the mapping process.

Primary implementation outcomes aligning with Proctor et al.’s framework [55] will be collected in Aim 2 (Task 5) to evaluate the resultant implementation strategy through a Hybrid Type III Design [56]. Chosen outcomes are penetration (i.e., degree to which school meals were provided equitably to low-income students) and cost (i.e., time, labor, supplies needed). Additional implementation outcomes include acceptability (i.e., degree of satisfaction); feasibility (i.e., practicality of strategy); and sustainability (i.e., maintenance of intervention) [57]. Secondary student-level outcomes will be assessed to understand behavioral impact of the implementation strategy on student weight status, family food security, and dietary behaviors. The EPIS framework will also support evaluation of key implementation determinants and processes over the evaluation period to triangulate implementation and behavioral outcome data.

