### Aim 1: use a community-engaged procedure to develop an equity-focused implementation strategy through a cluster randomized design

Informed by findings from the needs assessment (Task 1) [47], this aim will comprise identifying goals for implementation and objectives (Task 2), the development and tailoring of implementation strategies (Task 3), and implementation protocols (Task 4) for USM implementation through a cluster-randomized pilot design. From the schools in the needs assessment sample, two will be block randomized to receive implementation strategy selection support and two will implement USM as usual as a waitlist comparison group, before going through strategy development the following year (Fig. 2). Schools will not be blinded to this randomization given that they will be asked to sign a collaboration agreement and will be told whether they are completing mapping first or assigned to the waitlist condition. Eligible schools are those that have participated in our needs assessment or have agreed to collaboration through a formal agreement and are a public, non-charter school within the SDP.

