#### Analyses

Overall, the longitudinal data collection at baseline, 6 months, and 12 months following the inception of the trial will facilitate assessment of change over time and identification of factors that influence the outcomes. For the implementation outcomes, penetration will be analyzed by calculating the proportional change in number of low-income students participating in USM from prior to enacting the implementation strategy at baseline, 6 months, and 12 months following the start of the trial. For the costing measure, labor costs will be iteratively analyzed through the bottom-up approach to collect time and effort data from all implementing individuals; salary data will be obtained for all SDP positions through review of publicly available records. Receipts and invoices for all materials and miscellaneous costs will be analyzed. All costs will be calculated specific to each strategy to allow for accurate reporting and budget impact assessment showing net financial costs resulting from the strategies. The costconsequence analysis will be conducted to show the comparison of the costs and outcomes of each strategy in comparison to the waitlist condition (i.e., treatment as usual) [49, 72]. Data from the acceptability, feasibility, and sustainability surveys will be processed and aggregated at the school level to provide overall means. Interview data on other outcomes identified through the mapping procedure will be analyzed deductively through the GTE and Proctor outcomes framework [7, 57] followed by mapping ongoing determinants to the EPIS framework in the Implementation and Sustainment phases, providing tangible barriers and facilitators across the trial period [53]. This will enhance continuation of determinants analysis from Aim 1 and support adaptation/tailoring of the implementation strategies over time in response to needs/challenges at each school. Such adaptation is recommended by implementation science experts as a means to enhance equity through collaborations with community and clinical partners [43].

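### The cost measure covers only the strategies that mapping produces, while the randomised contrast with waitlist also includes the mapping support and monthly coaching, which have no cost line

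*Protocol article*

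**What the plan says.** **What is randomised.** Of four schools, "two will be block randomized to receive implementation strategy selection support and two will implement USM as usual as a waitlist comparison group" (Aim 1). The Background treats mapping as part of what is tested: "This pilot intervention will utilize an evidence-based process (i.e., implementation mapping"; the same sentence names penetration and cost as the primary implementation outcomes. Participants and procedures adds: "Intervention school teams will receive coaching during the implementation phase with monthly check-in meetings".

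**What is costed.** The scope is set in three places.
- The opening of Aim 2 announces a measure of the financial cost of each implementation strategy.
- Data collection and primary outcomes says the team will "measure the costs for each implementation strategy that results from the mapping process". Time and effort are to be captured for the people implementing at the school sites, and the results are to inform the value of each strategy and its potential for scale-up.
- The Aim 2 Analyses section ties every cost to a particular strategy, states that "salary data will be obtained for all SDP positions through review of publicly available records", and compares the costs and outcomes of each strategy with the waitlist condition.

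No section lists mapping meetings, facilitation or coaching as a cost item.

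**The concern.** The arms differ by three things together: mapping support, coaching, and the strategies that follow. Any difference in outcome from waitlist belongs to all three. The cost side is confined to the third. Mapping comes before the strategies and generates them, so its cost does not arise from any single strategy, and facilitation and coaching are delivered by the research team rather than by district employees.

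A cost-consequence table built this way pairs the outcomes of the package with a partial cost. The budget impact and scale-up conclusions inherit the gap. The Summary offers the mapping procedure itself as a product of the project and the findings as a model for other districts. A district that repeats the procedure would need facilitation and coaching from somewhere, and the figures would not show what that takes.

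**Working it through.** The article states no cost figure, so there is nothing to reproduce. The check sets the randomised contrast against the costing scope, then sizes the items without a cost line from the article's own quantities.

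**Contrast against scope**

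| Component separating the arms | Cost line in the article? |
|---|---|
| Mapping meetings: research-team facilitation and preparation | None |
| Mapping meetings: school staff attendance | None; it precedes any strategy |
| Monthly coaching: research-team delivery | None; wage source covers district posts only |
| Monthly coaching: school staff time | Possibly, as implementers' time and effort |
| Resulting strategies | Yes |

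**Inputs**
- Mapping meetings: about 5 per school (Recruitment and engagement), about 1.5 h each (Aim 1, Analyses).
- Check-ins: 15 to 30 min each (Participants and procedures); 18 in total, 9 per year (Table 1).
- Attendees: at least 3 representatives plus students per school (Recruitment and engagement). Four to five people is my assumption.

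**Per intervention school**
- Facilitated meeting time, per facilitator present: 5 × 1.5 h = 7.5 h.
- Coaching contact over one year: 9 × 0.25 h = 2.25 h to 9 × 0.5 h = 4.5 h.
- Coaching contact over two years: 18 × 0.25 h = 4.5 h to 18 × 0.5 h = 9 h.
- Attendee time, all roles: 4 × 5 × 1.5 h = 30 h to 5 × 5 × 1.5 h = 37.5 h.
- School staff share of that, if two or three of the attendees are staff (an assumption): 2 × 7.5 h = 15 h to 3 × 7.5 h = 22.5 h.

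**Both first-wave schools**
- Facilitated time: 2 × 7.5 h = 15 h.
- Coaching contact: 4.5 to 9 h over one year, or 9 to 18 h over two.
- Attendee time: 60 to 75 h.

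The one-year coaching figure fits the waitlist comparison better, because the planned assessments end at 12 months and the waitlist schools begin their own strategy development the following year. Preparation, workbook development and travel come on top and cannot be sized from the article.

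**Direction.** Each missing item is zero or positive. If all stay out, this omission can only move the package cost downward.

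**The case against.** **The exclusion is inferred.** No sentence says that mapping or coaching costs are left out. The Aim 2 Analyses section also speaks broadly of all implementing individuals and of receipts for miscellaneous costs, and the costing instrument has still to be built with the advisory board and the district. A reader might infer that the plan deliberately excludes the support; the article does not say so. What stands against the objection is that the scope is stated positively, and narrowly, three times. The broader wording could take in some staff time and purchases, but it does not reach research-team delivery time.

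**The object of evaluation is the strategy.** The theoretical framework section says outcomes are collected "to evaluate the resultant implementation strategy through a Hybrid Type III Design", and the contributions statement speaks of scaling up strategies across the district. For a district adopting finished strategies, mapping may be a one-off cost and the recurrent strategy cost the useful figure. This stands as a reason to report that figure separately. It does not make a strategy-only cost the right partner for outcomes measured against waitlist.

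**The support may be small.** A reader might infer that the intervention's main input is uncosted. The documents do not support that: the strategies are not yet chosen and no total exists for comparison. Five attendees and two years of check-ins are likewise one scenario, not fixed quantities.

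**Perspective.** The plan describes financial cost and budget impact. Shadow wages for parents and students would bring in a wider perspective that it does not adopt. The attendance payments ("provide a $25 gift card per participant per meeting attended") appear in the same sentence as consent for data collection, so they may partly be research incentives. This objection stands, and neither item should be required.

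**Conclusion.** The point holds as a mismatch between the costing scope and the randomised contrast. As written, research-team facilitation and coaching time and school staff time in mapping meetings have no cost line, so the cost-consequence comparison with waitlist and the scale-up conclusion can, on this account, only err towards too low a cost.

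The hours above show that the omitted input is not zero, but the percentage understatement cannot be calculated without a total cost. The conclusion assumes that the costing manual, which is not shown, follows the scope stated in the article. The attendee range also rests on the assumed four to five people per school. Because cost is a named primary implementation outcome and the correction is cheap, the change should be made before the mapping meetings start.

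**What to change.** 1. Add a cost category for mapping and coaching support, alongside the strategy-specific categories.
2. Log research-team time for facilitation, preparation and coaching prospectively, together with school staff attendance, and value it at an equivalent wage. Leave out research-only tasks such as transcription and coding.
3. In the cost-consequence comparison with waitlist, use the package cost: support plus strategies.
4. In the budget impact analysis, show set-up support and recurrent strategy cost as separate lines, so that a district adopting finished strategies and one repeating the mapping can each read off the relevant figure.
5. State the costing perspective. Parent and student time and gift cards may appear as an optional separate line. With four to five attendees the cards come to 4 × 5 × $25 = $500 to 5 × 5 × $25 = $625 per school.

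The price is a time log for meetings already planned and a somewhat less favourable stated cost. No trial procedure changes. Hours not logged at the time would be hard to recover later.
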